#### Secondary outcome measures at short-term

Perioperative outcomes including blood loss, operative time, additional haemostatic sutures and complications.Menstruation characteristics, dysmenorrhea (visual analogue scale (VAS)), Quality of Life (QOL) using Short-Form-36 [26] and EQ-5D-5L [27, 28], societal reintegration (PROMIS Short-Form-8a [29]), sexual function using the Female Sexual Function Index (FSFI [30]), applied medical and/or surgical therapy because of gynaecological symptoms, all obtained through digital questionnaires, will be assessed at three and nine months follow-up.Ultrasound evaluation will be performed at three months follow-up using TVUS, in which RMT, adjacent myometrium thickness (AMT), presence of a niche (depth of ≥2mm), length, depth and width of the niche, presence of large niches (RMT < 50% of AMT, RMT <3mm) and niche volume will be measured.

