## Background

Caesarean section (CS) rates have increased from 14.5 to 27.2% in the last two decades in the Western world. [1] In 2016, 26.664 CSs were performed in the Netherlands, being 16.0% of the total number of deliveries. [2] The increasing CS rate has stimulated an interest in the potential long-term morbidity of a CS scar, such as uterine rupture or malplacentation. [3–7] Other less severe, but more prevalent long-term symptoms are gynaecological symptoms and subfertility.

Only recently, gynaecological symptoms such as painful menstruations and postmenstrual spotting have been associated with CSs. [8–10] These symptoms are considered to be related to a niche, defined as *“an indentation at the site of the caesarean scar with a depth of at least 2 mm”*, visible on transvaginal ultrasound (TVUS). [11] Two cohort studies reported a strong association between postmenstrual spotting and a niche: odds ratio (OR) 3.1; 95% confidence interval (CI) 1.5–6.3 [8] and OR 5.5; 95% CI 1.1–26.5. [10] In these studies, a niche was observed in 50 to 60% of the women after a CS, using transvaginal ultrasound. [8, 10] Spotting was correlated to niche volume and inversely correlated to the residual myometrium thickness (RMT). [8, 10]

In addition to the gynaecological symptoms, a niche may influence fertility. A recent meta-analysis reported that a CS on average reduced the probability of subsequent pregnancy with 9% (relative risk (RR) 0.91; 95% CI 0.87–0.95) in comparison to a vaginal delivery. [12] None of the included studies in this meta-analysis evaluated the relation between subsequent fertility and the presence of a niche. One of the hypotheses is that intra-uterine fluid or cervical mucus or blood accumulation in the niche are expected to hamper the penetration of sperm cells or impair embryo implantation. [13] Long-term follow-up will facilitate the evaluation of the association between uterine closure, niche development, accumulation of intra-uterine fluid and subfertility.

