### Statistical issues

#### Sample size calculation

We use a superiority design since we expect double-layer closure to be favourable. Literature for making reliable estimations on postmenstrual spotting in relation to niches is scarce. We have used baseline data from the HysNiche [19] and LapNiche [15] study. We estimate the mean number of spotting days to be 3.5 days/month in the total group. We consider a 15% reduction in the mean number of spotting days clinically relevant, which is 0.5 day/month reduction. Assuming a standard deviation (SD) of 3.4 and a two-sided significance level of 5%, a total of 1488 women need to be included to achieve a power of 80%. Increasing the sample size to take into account 35% of women unevaluable (due to drop-out, non-response or amenorrhoea) for the primary outcome, 2290 women need to be included.

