#### Data-analysis

Data-analysis will be performed according to the intention to treat principle and additional per protocol analyses will be performed. A test will be considered statistically significant when the two-sided test shows a *p*-value < 0.05. Baseline characteristics will be presented using percentages, means with SD and 95% CI or medians with interquartile ranges (IQR), where appropriate.

The primary outcome, number of days of postmenstrual spotting, will be presented for both groups as mean with SD or median with IQR, and presented in a Box-Whisker graph to show the distribution. Differences in primary outcome between the groups will be tested using the independent t-test in case of normal distribution (possible after transformation of the outcome) or Mann-Whitney U test. An adjusted analysis will be performed using linear regression analysis in which we adjust for factors on which randomisation was stratified and for baseline factors on which relevant differences are observed despite randomisation.

Dichotomous secondary outcomes will be presented as percentages and RR with corresponding 95% CI. *P*-values will be calculated using the chi-square test or, if the expected count for at least one cell is below 5, using the Fisher exact test. Normally distributed continuous variables will be presented as means with SD, and differences between the groups will be calculated with an independent t-test. Non-normally distributed continuous variables will be presented as medians with IQR and differences between the groups will be calculated with Mann-Whitney U test. The questionnaires will be analysed using the appropriate algorithms and usual presentation methods (FSFI, EQ-5D-5L, SF36, PROMIS SF8a, iMCQ, iPCQ).

Comparison of primary outcome between women receiving single- and double-layer closure will be done as secondary analyses within each of the following subgroups separately:Planned (without labour) or unplanned (in labour) CSEmergency CS or notPreterm (< 37 weeks gestational age) or term (≥ 37 week gestational age) CSPresence (> 3cm) or absence (≤ 3cm) of dilatationPlacenta praevia or notPresence or absence of specific maternal morbidity (e.g. diabetes, pre-eclampsia, haemolysis/elevated liver enzymes/low platelet count (HELLP) syndrome, immunodeficient women)Singleton versus twin pregnancyNatural cycle or hormonally induced withdrawal bleeding

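### Niche dimensions exist only in women with a niche, and the one stated rule for continuous outcomes most naturally compares them in a subset that the intervention is expected to change

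*Protocol article*

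**What the plan says.** The section on short-term secondary outcomes lists what the three-month ultrasound will measure. It names RMT, adjacent myometrium thickness, presence of a niche (depth of 2 mm or more), "length, depth and width of the niche, presence of large niches", and niche volume. Niche presence and niche size are thus separate outcomes.

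The Data-analysis section sends dichotomous secondary outcomes to a relative risk (RR) with a chi-square or Fisher test, and normally distributed continuous ones to a t-test. For the rest it states: "Non-normally distributed continuous variables will be presented as medians with IQR and differences between the groups will be calculated with Mann-Whitney U test". It has no rule for a measurement that does not exist in some women. Intention to treat is stated as the general principle.

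The Background reports that in two cohort studies "a niche was observed in 50 to 60% of the women after a CS", seen on transvaginal ultrasound. It also says that spotting correlates with niche volume. Under Strengths and limitations the authors expect fewer niches to develop after double-layer closure.

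**The concern.** A woman without a niche has no niche length, width or volume. The same holds for depth if an indentation under 2 mm is not recorded. The intention-to-treat sentence assigns her to an arm but gives her no value. If she has none, the two-group test runs only among women with a niche. Niche status arises after randomisation and is what the intervention is meant to alter, so the women left in each arm need not be comparable.

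What is at stake is the reading of the dimension results. The trial could report fewer niches with double-layer closure together with significantly larger ones. Because the document links niche volume to spotting, a reader could take the second result as harm even if no woman's niche had grown.

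**Working it through.** **Inputs from the document.** Niche threshold 2 mm; prevalence 50 to 60%; the test rule quoted above; 2290 women randomised 1:1, so at most 2290/2 = 1145 scanned per arm.

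**The plan's own figure.** There is none for niche dimensions. The only sample size is for spotting days: 2 × (1.960 + 0.8416)² × 3.4² / 0.5² = 726 per arm, or 1452 in total. The stated 1488 is close (1452 is 2.4% lower), and 1488/(1 − 0.35) rounds up to 2290. This point does not touch it.

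**Share without a value.** 1 − 0.60 = 40% to 1 − 0.50 = 50%. The prevalence is for plain transvaginal ultrasound. The trial adds saline or gel sonography when no niche is seen, so the share could be smaller.

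**Why the subset test can mislead.**
- Random prevention: if a share q of niches is prevented regardless of size, prevalence falls by the factor 1 − q. The size distribution among the remaining niches is unchanged, so the niche-only test sees nothing.
- Selective prevention: assume log-normal depth with log-SD 0.7 and 55% of single-layer women at 2 mm or more. The log-mean is ln 2 + 0.7 × 0.126 = 0.781. The share at 4 mm or more is Φ((0.781 − 1.386)/0.7) = 0.194, so 0.55 − 0.194 = 0.356 lie between 2 and 4 mm. Preventing a quarter of these lowers prevalence to 0.55 − 0.25 × 0.356 = 0.461. The niche-only median rises from 3.3 to 3.6 mm, although no woman has a deeper niche.

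**Simulation 1** (assumed: 800 scanned per arm, 55% control prevalence, log-normal depth, Mann-Whitney test; ranges cover repeat runs):

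| Effect of double-layer closure | log-SD | Niche-only test | All scanned, no niche = 0 | Niche presence |
|---|---|---|---|---|
| All depths 15% smaller | 0.7 | 43–47% power | 98% | 95% |
| All depths 15% smaller | 1.0 | 26–27% power | 81–84% | 76% |
| 25% of 2–4 mm niches prevented | 0.7 | wrong direction in 37–38% | 77–78% | 95–96% |
| 25% of 2–4 mm niches prevented | 1.0 | wrong direction in 41–43% | 41–42% | 77% |
| 35% of 2–4 mm niches prevented | 0.7 | wrong direction in 70–71% | not computed | not computed |
| 35% of 2–4 mm niches prevented | 1.0 | wrong direction in 69–71% | not computed | not computed |

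**Simulation 2** (assumed: all 1145 per arm scanned, an upper bound; log-SD 0.6; 500 runs; results at control prevalence 50% / 60%; mean niche-only depth, double versus single):
- 30% of 2–4 mm niches prevented: 3.68 vs 3.48 mm / 3.97 vs 3.73 mm; significant in the wrong direction in 49% / 71%.
- 20% of niches prevented at random: 3.47 vs 3.48 mm / 3.73 vs 3.73 mm; significant in about 5%, as under no effect.
- Every indentation 0.5 mm shallower: 3.49 vs 3.47 mm / 3.72 vs 3.73 mm; significant in about 2% / 7%.
- Every indentation 15% shallower: 3.25 vs 3.47 mm / 3.46 vs 3.73 mm; significant in the right direction in 68% / 82%.

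In this second set, scoring no niche as 0 gave a mean depth 0.31 to 0.55 mm lower with double-layer closure, significant in the right direction in at least 99.8% of runs.

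**The case against.** A reader might infer that the protocol prescribes a niche-only comparison. It does not. It is silent on whether women without a niche are scored 0 or left out, and scoring 0 with a Mann-Whitney test would fit the rule as written. Where the authors leave women out of the primary analysis (amenorrhoea), they say so; there is no such sentence here. Coding of this kind may also sit in an analysis plan that is not shown. This stands to the extent that the subset is the natural reading, not a stated fact. But no zero-scoring convention is given either, and the general rule suits these outcomes badly.

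A reader might also infer that the trial would miss a preventive effect. The document does not support that. Niche presence is compared separately by RR, and niche prevalence, not niche size, is the named secondary ultrasound objective. When a quarter of small niches was prevented, the presence comparison had more power than zero-scored depth (95–96% against 77–78% at log-SD 0.7; 77% against 41–42% at log-SD 1.0). At log-SD 0.7 nearly all wrong-direction results (36 of 37 percentage points) came in trials that also showed significantly fewer niches. This stands in full.

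Two further limits stand. Reversal appeared only under selective prevention of small niches. And the simulations concern depth, which might be recorded below 2 mm; length, width and volume were not simulated, though the argument applies to them most directly.

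**Conclusion.** The point holds in a limited form. As written, the rule most naturally tests niche dimensions in a post-randomisation subset, and such a test cannot carry a treatment claim. How far it misleads depends on how prevention works: a proportional reduction keeps its direction with less power, random prevention or a uniform shift shows nothing, and prevention of mainly small niches can reverse the sign. The percentages are illustrative. The log-normal shape, the log-SDs, the number scanned and the prevention mechanisms are assumptions, not figures from the document.

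Only secondary niche-dimension results are at risk. Niche presence remains the main test of prevention, and RMT, the primary analysis and the sample size are unaffected. The wording should still be settled before analysis.

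**What to change.** State in the analysis text how women without a niche enter each dimension outcome:

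- Report length, width, depth and volume among niche-positive women as descriptive only, without a p-value or treatment claim, next to niche prevalence in each arm.
- If a between-arm test of niche size is wanted, apply it to depth and volume in all scanned women as randomised. Enter no niche as 0, and use a rank-based test or a mean difference with a bootstrap confidence interval.
- Note that this comparison combines presence with size and can have less power than the prevalence comparison, so it supplements that comparison and does not replace it.

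The cost is wording only. The ultrasound data are already due to be collected.

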#### Cost-effectiveness outcomes

Costs will be measured using adapted versions of the iMTA Productivity Cost Questionnaire (iPCQ [31]) and iMTA Medical Consumption Questionnaire (iMCQ [32]) from a health care and societal perspective at nine months of follow-up.

#### Secondary outcome measures at long-term

Menstruation characteristics, pain, sexual functioning, QOL and social reintegration will be evaluated at three years follow-up.Reproductive outcomes at three years follow-up: % of women desiring to conceive, % of women that conceived including time to conceive, % of women with an ongoing pregnancy, the need for fertility treatment and pregnancy outcomes such as mode of delivery or complications will be determined.

Long-term outcomes will be presented in a separate article.

### Data collection and data management

#### Intraoperative data

Immediately after the CS we will register relevant items regarding the delivery and CS in an eCRF, in which confidentiality and anonymity are ensured and audit trails are accessible. These items include: reason for planned or unplanned CS, emergency CS or not, whether women experienced contractions, dilatation, performed method for uterine closure, endometrial saving technique applied, used suturing material, extra haemostatic sutures, operative time, blood loss and complications.

#### Collection of baseline characteristics and patient reported outcomes

Baseline characteristics will be collected through a digital questionnaire at 2–4 weeks after caesarean section, sent to the e-mail address of participants. Since we will also include unplanned CSs, we decided that it is not possible for all participants to answer questions regarding baseline characteristics before the operation. Baseline parameters include maternal age, body mass index, social economic status, smoking habit, medical and obstetric history, gestational age and previous vaginal deliveries, all reported by the participant. We expect that the impact of niche related symptoms such as postmenstrual spotting on daily activities and sexual behaviour may be influenced by ethnic background and religion, therefore we will also register these characteristics. At three months, nine months and three years follow-up, again digital questionnaires will be sent to participants to assess the primary and secondary outcomes (see Fig. 1). At nine months, we ask participants record their exact menstrual and spotting pattern, if any, in an adjusted menstruation score chart. [33] Reminders for all questionnaires will be sent every two weeks, with a maximum of three times. When no response is given after the reminders, research nurses from participating centres will be asked to call the participant.

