### Recruitment and randomisation

Eligible women will be asked by a gynaecologist, resident, clinical midwife or research nurse to participate in the trial when they undergo a planned CS. Eligible women who are planned to undergo a vaginal delivery will also be informed about this study during pregnancy in case they need an unplanned CS. Furthermore, women during induced labour and women receiving adequate therapy for pain during labour, will be asked to participate in case a CS is needed during labour for any indication.

When the decision of a CS is made and all selection criteria are met, women will be randomly allocated to single-layer (control group) or double-layer (intervention group) closure (1:1) (see Fig. 1). Randomisation will be performed using a web-based application ALEA 2.2 which displays a computer-generated random number, managed by the Clinical Research Unit of the Amsterdam UMC - location AMC. We will use a permuted block-design, stratified for recruiting centres and for planned or unplanned CS. All women that decline to participate will be registered anonymously in order to record the number and reason for refusal. Subjects who withdraw from this study will not be replaced. 

Gynaecologists, residents, clinical midwives or research nurses enrol participants and assign them to the intervention. The CS will be performed by either a gynaecologist, a resident supervised by a gynaecologist or by a resident that is authorised to perform CSs without supervision. Participants and sonographers will be blinded for the closure technique. If operative reintervention after CS is needed and the gynaecologist that performs the reintervention needs to know the closure technique that the participant was assigned to, unblinding is possible through the logistic trial coordinator. We expect this situation to occur very infrequently.

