**Fig. 1 Fig1:**
[figure not shown]
Flowchart of the 2Close study. * = baseline questions, EQ-5D-5L. ** = symptom questionnaire, EQ-5D-5L, SF36, PROMIS SF8a, iMCQ, iPCQ. *** = symptom questionnaire, FSFI, EQ-5D-5L, SF36, iMCQ, iPCQ. **** = symptom questionnaire, fertility questionnaire, FSFI, EQ-5D-5L, SF36, PROMIS SF8a

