#### Economic evaluation

The economic evaluation will be performed alongside the RCT from a societal perspective. Both a cost-effectiveness and cost-utility analysis will be performed with a time horizon of nine months to relate the difference in societal and healthcare costs between double-layer and single-layer unlocked uterine closure during a CS to the difference in clinical effects. Healthcare costs include costs of primary and secondary care, complementary care and home care. Costs in other sectors include presence and absence from paid and unpaid work. The friction cost approach will be used to estimate indirect costs. For the valuation of health care utilization standard prices published in the Dutch Costing guidelines will be used. [34] Medication use will be valued using prices of the Royal Dutch Society for Pharmacy.

Societal costs will be related to the following effect measures in the economic evaluation: days with postmenstrual spotting and quality-adjusted life-years (QALYs) based on the Dutch tariff for the EuroQol (EQ-5D-5L). [27, 28, 35]

We hypothesise that double-layer uterine closure will reduce postmenstrual spotting and related consultations for gynaecological or fertility related problems and applied therapies, and as a consequence that it will be cost-effective in comparison with single-layer uterine closure.

The analysis will be done according to the intention to treat principle. Missing costs and effect data will be imputed using multiple imputation. Incremental cost-effectiveness ratios (ICERs) will be calculated by dividing the difference in mean total costs between the treatment groups by the difference in mean effects. Bootstrapping with 5000 replications will be used to estimate 95% CI around cost differences and the uncertainty surrounding the ICERs. Uncertainty surrounding the ICERs will be graphically presented on cost-effectiveness planes. Cost-effectiveness acceptability curves showing the probability that double-layer uterine closure is cost-effective in comparison with single-layer uterine closure for a range of different ceiling ratios will also be estimated. Adjustment for confounders and effect modifiers will be done if necessary. [36]

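### The EQ-5D-5L grouped with baseline is very probably measured 2–4 weeks after the randomised operation, and neither adjustment rule excludes it

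*Protocol article*

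**What the plan says.** All references are to the protocol article.

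- **Order of events.** Under Recruitment and randomisation: "When the decision of a CS is made and all selection criteria are met, women will be randomly allocated to single-layer" or double-layer closure. Allocation therefore precedes surgery.
- **Timing of baseline.** Under Collection of baseline characteristics and patient reported outcomes: "Baseline characteristics will be collected through a digital questionnaire at 2–4 weeks after caesarean section". The reason given is that, with unplanned operations included, "it is not possible for all participants to answer questions regarding baseline characteristics before the operation".
- **Content of the baseline set.** The Fig. 1 legend gives the first questionnaire set as "baseline questions, EQ-5D-5L". No preoperative EQ-5D-5L is described anywhere.
- **Outcome times.** Under Secondary outcome measures at short-term, quality of life and the other questionnaire outcomes "will be assessed at three and nine months follow-up". The long-term list adds three years. The 2–4 week point is in neither list.
- **Use of the instrument.** Under Economic evaluation, costs over nine months are related to spotting days and to "quality-adjusted life-years (QALYs) based on the Dutch tariff for the EuroQol (EQ-5D-5L").
- **Adjustment.** Under Data-analysis, the adjusted linear regression of the primary outcome includes the stratification factors and allows "for baseline factors on which relevant differences are observed despite randomisation". Under Economic evaluation: "Adjustment for confounders and effect modifiers will be done if necessary".
- **Acknowledged limitation.** Strengths and limitations treats the late baseline questionnaire as a source of recall bias and mentions no other problem.

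**The concern.** Collecting age, obstetric history or gestational age a few weeks late is harmless to the comparison, because closure technique cannot alter them. Health status at 2–4 weeks is different. It is measured after the randomised treatment and may respond to it. A difference between arms at that point may be an early treatment effect, not a chance imbalance, and recall bias does not describe that problem.

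Once the value is called baseline, two adjustment rules could reach it. Conditioning on a variable that treatment has affected removes part of the effect being estimated, and prespecifying the adjustment would not cure this. The exposure is greatest in the cost-utility analysis, where the same instrument supplies the QALYs. The spotting rule matters less: it governs only an adjusted analysis that supplements an unadjusted test.

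**Working it through.** **1. Is the EQ-5D-5L really in the 2–4 week questionnaire?** The figure itself is not shown. The legend describes four questionnaire sets, and the data-collection section gives four questionnaire times: 2–4 weeks, three months, nine months and three years. The fertility questionnaire appears only in the fourth set, which fits the three-year reproductive outcomes. Matching in order puts the first set, with the EQ-5D-5L, at 2–4 weeks. This is an inference, but a strong one.

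**2. Inputs for an illustration.** The plan gives no early utility difference, so there is no figure of its own to reproduce. From the documents: assessment at t = 2, 3 or 4 weeks, later assessments at three and nine months (13 and 39 weeks), and a nine-month horizon. Assumed:
- one arm has a utility deficit d of 0.01 to 0.05, constant from surgery to week t, then falling linearly to zero at week 13;
- the 2–4 week value has the same correlation ρ with the three- and nine-month utilities within each arm, with equal SDs.

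**3. Loss under the assumed course.** (t·d + 0.5·(13 − t)·d)/52 = d·(13 + t)/104.

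**4. Value placed at time zero, no adjustment.** 0.5·13·d/52 = 0.125d.

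| t (weeks) | Assumed loss | At time zero, unadjusted | Share missed |
|---|---|---|---|
| 2 | 15/104·d = 0.144d | 0.125d | 2/15 = 13.3% |
| 3 | 16/104·d = 0.154d | 0.125d | 3/16 = 18.8% |
| 4 | 17/104·d = 0.163d | 0.125d | 4/17 = 23.5% |

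The assumed loss runs from 0.0014 QALY (d = 0.01, t = 2) to 0.0082 (d = 0.05, t = 4). The unadjusted figure runs from 0.00125 to 0.00625.

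**5. Value placed at time zero and also used as a covariate.** The trapezoid weights on the three utilities are 0.5·13/52 = 0.125, 0.5·39/52 = 0.375 and 0.5·26/52 = 0.25. The regression slope of the QALY on the first value is 0.125 + ρ·(0.375 + 0.25) = 0.125 + 0.625ρ. The adjusted loss is 0.125d − (0.125 + 0.625ρ)·d = −0.625ρ·d. A negative loss is an apparent gain for the arm with the worse early recovery.

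| ρ | Adjusted result | d = 0.01 | d = 0.05 |
|---|---|---|---|
| 0 | no difference | 0 | 0 |
| 0.3 | gain 0.1875d | 0.0019 | 0.0094 |
| 0.5 | gain 0.3125d | 0.0031 | 0.0156 |
| 0.7 | gain 0.4375d | 0.0044 | 0.0219 |

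**6. Value placed at its actual time, with a common time-zero utility.** Joined by straight lines, the difference is a triangle of height d over 13 weeks: 0.5·13·d/52 = 0.125d, as in step 4. The common starting value cancels from the difference between arms. The 13–23% shortfall therefore depends on the path assumed between surgery and the first measurement. Carrying the measured difference back to surgery restores step 3.

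**The case against.** The case against is substantial, and much of it stands.

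- **No stated covariate.** The listed baseline parameters are demographic, medical and obstetric items, and the EQ-5D-5L is not among them. The legend puts it beside the baseline questions. A reader might infer that the plan will adjust early harm away. The text does not say so; it only fails to rule it out.
- **Reach of the Data-analysis rule.** It applies to spotting days at nine months. It cannot remove an EQ-5D-5L difference from the QALYs.
- **Meaning of a confounder.** A postoperative utility altered by closure is not a confounder, so a careful analyst would leave it out under the Economic evaluation rule. That is fair, but the baseline label invites the opposite choice.
- **Starting value.** A reader might infer that using the measurement as the QALY starting point hides the loss. At t = 3 it keeps 0.125/0.154, about 81%. Only covariate adjustment removes or reverses it.
- **Early harm recorded elsewhere.** Blood loss, operative time, extra haemostatic sutures and complications are secondary outcomes, and serious adverse events are followed. Early harm is not hidden from the trial. What is at risk is its patient-reported utility, the part that enters the QALYs.
- **Size.** The Background regards double-layer closure as safe in the short term, so d may be small.

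The argument that covariate lists belong in a fuller document does not dispose of the point. The article itself groups a post-treatment measurement with baseline, and the feasibility reason explains why no preoperative value exists without turning a postoperative one into a baseline.

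**Conclusion.** The point holds as a mislabelled measurement combined with adjustment rules that do not exclude it. It rests on reading the legend together with the data-collection section, which is very probably right.

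The consequence is conditional. As a covariate in the QALY analysis, the value could remove an early utility effect or reverse it, by up to 0.022 QALY in the illustration. As an unadjusted time-zero value it would understate the assumed loss by roughly 13–23%. The size in this trial is unknown, because d, ρ and the shape of recovery are all assumptions. It would be wrong to conclude that the cost-utility result is biased as planned.

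The unadjusted primary comparison, the sample size, which is built on spotting days, and the perioperative outcomes are unaffected.

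**What to change.** 1. Label the 2–4 week EQ-5D-5L as the first follow-up measurement and report it by arm.
2. In the nine-month QALY curve, place it at its actual assessment time, with the same time-zero utility in both arms, justified by randomisation. The documents give no such value, so state it as an assumption and vary it in a sensitivity analysis. Because a common value cancels from the arm difference, also vary the path from surgery to the first measurement, including carrying the observed difference back to surgery.
3. In Data-analysis and Economic evaluation, restrict adjustment to the stratification factors and to characteristics that closure technique cannot change. Name the 2–4 week EQ-5D-5L as excluded.
4. In Strengths and limitations, add that this measurement is post-randomisation, alongside the recall point.

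The cost is wording and minor analysis work. No new data are needed.
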